### Interventions

3.4

#### START NOW adapted

3.4.1

The intended low-threshold intervention START NOW promotes resilience, which refers to good developmental outcomes despite exposure to significant adversity (40). The existing START NOW training includes a manual with detailed instructions for group facilitation and a workbook for participants (22). The sessions consist of exercises and discussions wherein participants will learn skills and tools and will have the opportunity to practice, ask questions, and discuss the topics and approaches. The program combines aspects of cognitive behavioral therapy (CBT), motivational interviewing (MI), dialectical behavior therapy (DBT), acceptance and commitment therapy (ACT) and trauma-sensitive care (22). Studies in different contexts have shown START NOW’s effectiveness in terms of reducing oppositional and aggressive symptoms (41), reducing hospitalization rates (42), improving mental health functioning (43) and increasing satisfaction rates (44). There is a need to culturally adapt this existing intervention, which has previously been used with Western populations, since effective psychological interventions are rooted in a cultural context and must be consistent with clients’ cultural beliefs (45). Moral and ethical obligations therefore dictate that mental health practitioners take into account cultural contexts and values relevant to the well-being of clients (46). The same applies to the development of interventions, as cultural adaptation positively affects the outcome of treatment and has shown to be more effective compared to conventional Western, bona-fide interventions (47, 48). Effective interventions can use culturally sensitive approaches that avoid pathologizing refugees’ experiences and instead honor cultural systems and values to promote recovery and resilience processes (18).

Meta-analyses have shown that the effectiveness of adapted interventions increases with the number of adaptation elements implemented (49). According to Kananian et al.’ (50) proposal of deep structural adaptations used in the development of Culturally Adapted Cognitive Behavioral Therapy (CA-CBT) for PTSD (51), different elements can be divided into specific and unspecific components, surface adaptations, mode of delivery, translation, and adaptation of materials. Specific components include adapting session content to the refugee experience and using positive imagery to overcome cultural barriers (52). Unspecific components refer to cultural concepts of distress, including explanatory models (i.e., aetiological assumptions) and idioms of distress (i.e., the expression of symptoms) (53).

Regarding specific components in START NOW Adapted, we will adapt both the workbook for participants as well as the manual for facilitators by including exemplary experiences of young refugees instead of the original ones. In order to capture these experiences, we will gain insights from social workers who work directly with young refugees. It is important that the facilitator conveys that these experiences are exemplary and that everyone has individual but possibly similar experiences. Positive images, such as different weather conditions or a color palette drawn to describe the current emotional state, serve as an easier introduction to the topics. With regards to unspecific components, previous research has shown that emotions are understood differently in different cultures (53). Therefore, explanations in the workbook and manual will be kept to a minimum. The facilitators are instructed to ask about the individual understandings in their groups and to include the young people’s explanations in the training.

Superficially, the comics and characters will be adapted to represent more diverse cultures and better opportunities for identification.

Regarding the mode of delivery, group-based interventions have shown to be a successful method for mental health intervention among refugee populations (19). Therefore, START NOW Adapted will be led by 10 group discussions with a manual guiding the facilitators through the sessions. The facilitator is a trained individual from the same cultural background and supervised by a START NOW member of the research team.

All materials will be translated into German, English, Turkish, Persian, Ukrainian and Arabic.

In the introduction, participants learn about emotions and are introduced to the START NOW skills. These skills, called SLOW DOWN, TAKE A STEP BACK, ACCEPT, RESPECT and TAKE ACTION, are strategies or techniques that can be used to better manage stress and difficult emotions. Participants will also get to know six fictional teenagers who are often stressed and get into trouble because they cannot regulate their emotions. During the sessions, the teenagers will be used as examples to illustrate situations.

In the second session, participants are introduced to the ABC model of rational-emotional behavior therapy (Adverse Event - Beliefs - Consequences) and learn that every feeling has an important purpose. In the third session, participants learn about the importance of mindfulness and do a mindful breathing exercise (SLOW DOWN). In the fourth session, participants are invited to step back from negative thoughts. They learn to observe them and to identify errors in thinking (TAKE A STEP BACK). In the fifth session, they learn to accept their negative feelings instead of fighting them, so that they do not get in the way of their goals. Participants are also guided to define goals and values that are important to them (ACCEPT). In the sixth session, participants learn that respect for themselves is an important prerequisite for recognizing when their own needs are being violated, and that respect for others is important for having good relationships and friendships. They check themselves for unequal relationship patterns and are given tips on how to set their own limits and not overstep them with others (RESPECT). In the seventh session, participants are taught to take action to achieve their goals by identifying obstacles and dividing them into things they can change and things they cannot (TAKE ACTION). In the eighth session, participants are given additional skills to regulate their emotions by not letting them reach dangerous levels and by observing their early warning signals.

Sessions 9 and 10 explicitly target anxiety and depression. Participants learn which unhelpful strategies they might use to cope with anxiety and how to manage anxiety using the START NOW strategies they have learned in the previous sessions. In the last session on depression, mechanisms are described to conquer depressive feelings, for example by acting in the opposite way to how they feel at that moment or identifying thought errors.

#### Treatment as usual

3.4.2

The treatment as usual (TAU) group will receive their usual treatment. We will evaluate any potential modifications in treatment as usual for participants throughout the study, which will be considered during the statistical analysis or possibly lead to the exclusion of the case. Following the conclusion of the study, participants in the TAU group will have the option to receive the intervention START NOW Adapted for ethical reasons and to increase study-related commitment.

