### Study design

3.1

The study is a confirmatory, randomized controlled trial with two arms that takes place in a monocentric, national setting and assesses effectiveness.

To evaluate feasibility, qualitative semi-structured interviews will be conducted with specialists working with refugees prior to the intervention study. These interviews will follow an inductive and explorative approach and involve staff from institutions such as asylum centers and dormitories for unaccompanied minors. To estimate the feasibility and effectiveness of this trial, specialists will be interviewed about their daily challenges, language and cultural barriers, as well as potential difficulties with the implementation and adaptation of START NOW. The inclusion of qualitative information can help to better understand how a complex intervention such as START NOW can work and aid in the adaptation process of the intervention (31).

After the conduction of these interviews, possible participants taking part in the intervention study are screened for eligibility. For those who are eligible, the study duration will be 6 months, including three assessments (shown in Figure 1): a baseline assessment (t1), a post-treatment assessment (t2), and a 12-weeks follow-up assessment (t3). In case a participant has missed a session, they will be marked as absent and the number of sessions will be taken into consideration in the data analysis. To minimize bias, participants will be randomly assigned to one of two experimental group conditions, (1) group skills training using an adapted version of START NOW, (2) TAU. Randomization should take place within 2 weeks before the intervention, after the baseline assessment (t1) has been conducted. Between t1 and t2, the intervention phase takes place over a period of 10 weeks, with one session per week for each group. The study takes place in a group setting since conducting mental health interventions via group workshops, which aim to enhance social interaction was observed to have a positive impact on participants’ mental health (19). For ethical reasons and to increase study-related commitment, participants in the control group (receiving TAU) as well as non-eligible participants will be offered the chance to receive treatment after the study concludes.

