After informed consent has been given, participants will be screened for eligibility. Any participants can withdraw from the study at any time without personal disadvantages and without having to give a reason. The applicants can also decide about termination of treatment in case of protocol violations or if the applicants believe continuation in the study would be detrimental to the participants` well-being. If participants withdraw their participation prior to randomization, other eligible individuals can move up. Premature withdrawals in the group training will not be replaced after the beginning of the intervention. Relevant additional treatments (e.g., individual psychotherapy) administered to the participant upon entry to the trial or at any time during trial participation are regarded as concomitant treatments and will be documented as well as concomitant medication.

After the screening process, eligible persons will be notified by the project management through their institution about their participation opportunity. If someone is not eligible, both the institution as well as the individual will be notified online via mail. If eligible participants still wish to take part, they are randomly assigned to a group. In general, randomization will be done within each institution by randomly assigning participants to either the intervention or control group using computer algorithms. If not enough adolescents within an institution wish to participate, we will make an adjustment to the general randomization process by creating cross-institutional groups. Participants will be randomized in separate steps for each gender group. In this way, we ensure a random distribution between the intervention and control groups within each gender group and a safe environment for all participants. This is in tune with cultural norms and expectations of the target population, and this way, our results are more likely to provide important insights around cultural idioms of distress that may be gender specific (32).

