### Statistical analyses

4.2

For statistical analyses, we will use R with its graphical user interface R Studio. The significance level will be 0.05 for all analyses. An effect of at least moderate size will be considered as clinically relevant. To test our hypotheses, we will use multilevel models with primary and secondary outcome measures as dependent variables (three individual models for depression, perceived stress, and emotion recognition), and with timepoint (baseline, post-treatment, follow-up) and intervention condition (START NOW vs. TAU) including their interaction as independent variables. A significant interaction between intervention condition and time suggests a difference in symptom change depending on treatment group. In case of significant main or interaction effects, we will evaluate post-hoc contrast considering time and intervention condition. Treatment group will be added as level two in the multilevel framework.

Using multilevel models will allow to analyze data on the observational level, which provides more information in contrast to calculating change scores or using repeated measures ANOVA, increasing measurement accuracy and power. In addition, multilevel mixed models can handle missing observations and allow to examine random effects at the intercept and slope level. Furthermore, we will test model improvement when considering quadratic versus linear trends for time, random effects for time, and correlation structure between timepoints. Covariates, including participant age, gender, and post-migration stress will be added if they differ between intervention groups. On group level, possible covariates include facilitator, institution or cultural background.

To analyze perceived stress and resilience as potential mechanisms in treatment success, we will use bias-corrected bootstrap mediation models with intervention condition as predictor, change in symptoms of depression as outcome, and change in stress/resilience as mediator. Change in symptoms of depression and indicators of stress/resilience will consist of participant’s random slope for time extracted from the multilevel mixed models depending on results of the first hypothesis.

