### Limitations

5.2

One of the challenges of this project may be self-selection bias if certain refugees are more likely to volunteer for the intervention. This could affect the generalizability of the results to the wider refugee population. To reduce this bias, we offer high, but still appropriate, incentives of 20 CHF in vouchers for each assessment (t1 – t3). There also may be differences in the delivery of the intervention or usual care between facilitators. To counteract this bias, all facilitators receive extensive pre-training that provides the same content to all. Additionally, facilitators will be included as possible influences at level two in the multilevel framework.

Another limitation is the lack of blinding among participants and facilitators, a frequent cause of bias in RCTs that include non-pharmacological interventions. Known problems associated with lack of patient blinding, such as response bias with self-reported outcomes, relate primarily to studies with a predominantly explanatory aim (66). For instance, attrition rates may be simultaneously regarded as both sources of bias and outcomes influenced by the intervention (66). It is therefore important to understand and address the reasons for dropout. In multilevel models, a sub-model accounts for missing data. The selection model improves the analysis of growth curves by using logistic regressions to show how likely it is to have missing data at each time. Meanwhile, the pattern mixture approach looks at each group of missing data separately and then combines the results (67). Thereby, multilevel modeling makes use of all available information without needing to resort to list wise deletion. Another method of minimizing bias is that only well-validated questionnaires will be used during assessments.

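### The plan permits randomised participants to be excluded, at discretion and without a criterion, because their usual treatment changed during the study

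*Protocol article*

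**What the plan says.** All references are to the protocol article.

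- **Treatment as usual (3.4.2):** "We will evaluate any potential modifications in treatment as usual for participants throughout the study", and these changes are ones "which will be considered during the statistical analysis or possibly lead to the exclusion of the case". No criterion, time point or decision-maker is given.
- **Study design (3.1):** "The study is a confirmatory, randomized controlled trial with two arms"; the same sentence says that it assesses effectiveness. On timing: "Randomization should take place within 2 weeks before the intervention, after the baseline assessment (t1) has been conducted". On missed sessions: absences are recorded and "the number of sessions will be taken into consideration in the data analysis".
- **Study procedure (3.2):** additional treatments, at entry or during participation, "are regarded as concomitant treatments and will be documented as well as concomitant medication". No exclusion is attached.
- **Statistical analyses (4.2):** the models are specified "with timepoint (baseline, post-treatment, follow-up) and intervention condition (START NOW vs. TAU) including their interaction as independent variables". Age, gender and post-migration stress are possible covariates, with facilitator, institution and cultural background at group level. Changes in care and number of sessions appear in neither list.
- **Limitations (5.2):** "multilevel modeling makes use of all available information without needing to resort to list wise deletion".

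No section says that participants are analysed in the arm to which they were randomised.

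**The concern.** A change in usual treatment during the study happens after allocation. A participant who gets worse may be given more care, and one who gains access to care may improve. Either way, the participants removed may differ in outcome from those kept, and the remaining groups are no longer those that randomisation made comparable. Because no criterion is written down, the decision could also be taken with outcomes in view.

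The clause also changes the question. Usual care in practice includes people starting, stopping or switching treatment. A control group from which those people have been removed is not usual care but usual care that happened to stay constant. That sits badly with an effectiveness trial, and with the Eligibility criteria section, which says the design follows regular clinical practice.

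This is more than a detail left to an analysis plan. The article states the option to exclude, and an analysis plan that followed it faithfully would carry it forward.

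**Working it through.** **Reading the sections together**

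1. Randomisation follows the t1 assessment and precedes the intervention (3.1). Care changes are evaluated throughout the study (3.4.2). Exclusion on this ground can therefore rest on events after randomisation.
2. Two responses to a care change are offered, analytic handling or exclusion, and nothing says which applies when (3.4.2).
3. The Limitations section relies on models that use all available data and avoid discarding cases. It also notes that attrition can be both a source of bias and a result of the intervention. The same reasoning applies to investigator-made exclusions.

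**Size (illustration only)**

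The plan states no figure that depends on this clause, so there is none to reproduce. Let p be the share of controls excluded and δ the difference in mean outcome between excluded and retained controls. The mean of all controls is (1 − p) × retained mean + p × excluded mean, so dropping the excluded cases moves the control mean by p × δ.

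Assumed inputs, none of them in the document: p = 10–30%, δ = 0.5–1.0 SD.

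- Smallest: 0.10 × 0.5 = 0.05 SD
- Largest: 0.30 × 1.0 = 0.30 SD

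If the rule covers both arms, the distortion is p × δ in the control arm minus p × δ in the intervention arm. It cancels only if the two products are equal. With δ = 1.0 SD in both arms and 20% against 10% excluded, it is 0.20 − 0.10 = 0.10 SD.

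A simulation gives a similar picture. It assumed 40 per arm, a standardised outcome, 10–30% of controls excluded, and a latent correlation of 0.3–0.7 between doing worse and having care changed (4,000 runs per setting):

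| | All randomised kept | Controls excluded |
|---|---|---|
| No true effect: estimated difference | about 0 | 0.06 to 0.35 SD against the intervention |
| No true effect: two-sided type I error | about 0.05 | 0.06 to 0.31 |
| True benefit 0.5 SD (assumed): estimated benefit | about 0.50 SD | 0.44 down to 0.15 SD |

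If instead the excluded controls were those who improved with added care, then with no true effect the same distortion would, by symmetry, favour the intervention.

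**Number of sessions**

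Controls are offered the training only after the study, so their count is 0 by design. In a model with outcome = a + b × condition + c × sessions, b is the contrast at zero sessions, while the randomised contrast is b + c × mean sessions attended. The two agree only if c × mean sessions is zero. This matters only if sessions enter the primary model, which section 4.2 does not say.

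**The case against.** The clause is permissive, offers analytic handling first, and could be meant to define a per-protocol set. A condensed article commonly leaves analysis populations to a later document. That is fair as far as it goes: the absence of a named population is not the point. But the clause is not tied to a secondary set, and as written it allows exclusion from any analysis, including the primary one.

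Several stronger readings are tempting, and the document does not support them:

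- **That the rule applies to controls only.** It stands in the TAU section, but it speaks of participants generally, and the next sentence specifies the TAU group when it means controls. One arm or both remains open.
- **That it contradicts the Study procedure section.** Documenting additional treatment there and considering it in the analysis here are compatible steps. Documentation does not rule out exclusion.
- **That exclusions would be made unblinded.** The Limitations section reports lack of blinding for participants and facilitators. It does not say who would decide on exclusions.
- **That the planned use of sessions already breaks the randomised comparison.** The Study design section does not say that sessions enter the primary model, and section 4.2 does not list them. A dose or complier analysis would fit the text.
- **That a false claim of benefit is the likely result.** The direction depends on who is excluded. In the simulated pattern the bias runs against the intervention.

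The assumed exclusion shares and outcome differences have no anchor in the document. The f = 0.25 in the Sample size section refers to a within-between interaction and is not converted here into a benchmark in SD units.

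**Conclusion.** The point holds for the exclusion clause. A trial described as confirmatory should not keep an open option to remove randomised participants because of what happened to their care afterwards. This conclusion rests on the wording and the timing alone. It holds whether the clause covers one arm or both, although the direction and size of any bias depend on that and on who is excluded.

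The 0.05–0.30 SD range and the simulation results are illustrations under assumed inputs. They show that the distortion need not be trivial; they do not predict it.

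The session count is a clarification only. The Study design and Statistical analyses sections need to be aligned so that attendance cannot be read into the primary model.

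**What to change.** - In section 3.4.2, delete the option of excluding the case.
- State that the primary analysis includes every randomised participant in the assigned arm, regardless of changes in usual or concomitant treatment.
- State that changes in care are reported by arm and used only in a labelled sensitivity analysis, with the same rule for both arms.
- In sections 3.1 and 4.2, state that the number of sessions is used only in a secondary analysis, either a complier-average effect or a dose analysis within the intervention arm.

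The cost is a few sentences. No new data are needed, since section 3.2 already has concomitant treatment documented and section 3.1 has absences recorded. The change should be made before outcome data are examined.
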